## Abstract

**Background:**

Numerous smartphone apps are targeting physical activity and healthy eating, but empirical evidence on their effectiveness for initialization and maintenance of behavior change, especially in children and adolescents, is still limited.

**Objective:**

The aim of this study was to conceptualize a theory-based and evidence-based mHealth intervention called SMART*FAMILY* (SF) that targets physical activity and healthy eating in a collective family-based setting. Subsequently, the app will be refined and re-evaluated to analyze additional effects of just-in-time adaptive interventions (JITAIs) and gamification features.

**Methods:**

A smartphone app based on behavior change theories and behavior change techniques was developed and implemented and will be evaluated with family members individually and cooperatively (SF trial). Existing evidence and gained results were used to refine and will be used to re-evaluate the app (SF2.0 trial). Both trials are cluster randomized controlled trials with 3 measurement occasions. The intervention group uses the app for 3 consecutive weeks, whereas the control group receives no treatment. Baseline measurements (T_0_) and postintervention measurements (T_1_) include physical activity (ie, self-reported and accelerometry) and healthy eating measurements (ie, self-reported fruit and vegetable intake) as the primary outcomes. The secondary outcomes (ie, self-reported) are intrinsic motivation, behavior-specific self-efficacy, and the family health climate, complemented by an intentional measure in SF2.0. Four weeks following T_1_, a follow-up assessment (T_2_) is completed by the participants, consisting of all questionnaire items to assess the stability of the intervention effects. Mixed-method analysis of covariance will be used to calculate the primary intervention effects (ie, physical activity, fruit and vegetable intake) while controlling for covariates, including family health climate, behavior-specific self-efficacy, and intrinsic motivation.

**Results:**

This study is funded by the German Federal Ministry of Education and Research and ethically approved by the Karlsruhe Institute of Technology. For both trials, it is hypothesized that the apps will positively influence physical activity and healthy eating in the whole family. Furthermore, SF2.0 is expected to produce stronger effects (ie, higher effect sizes) compared to SF. SF app development and piloting are completed. Data acquisition for the SF trial is terminated and discontinued due to the COVID-19 pandemic. SF2.0 app development and piloting are completed, while data acquisition is ongoing. Participant recruitment for the SF 2.0 trial started in February 2020. The results for SF are expected to be published in mid-2021, and the results of SF2.0 are expected to be published in mid-2022.

**Conclusions:**

In this study, it is hypothesized that targeting the whole family will facilitate behavior change at the individual level and the family level, as the implemented strategies address changes in daily family life. Furthermore, subsequent app development (SF2.0) with supplementary addition of motivation-enhancing features and a JITAI approach is expected to enhance positive intervention effects.

**Trial Registration:**

German Clinical Trials Register DRKS00010415; https://tinyurl.com/yyo87yyu

**International Registered Report Identifier (IRRID):**

DERR1-10.2196/20534

## Introduction

### Background

A lack of physical activity, too much sedentary behavior (eg, extended screen time and nonactive media usage), and an unhealthy diet are serious concerns of modern societies. These behaviors increase the risk of health conditions across all ages [1-4]. Research has shown that many children and adolescents do not sufficiently engage in physical activity [5] and frequently make unhealthy food choices [6,7]. Approximately 81% of the children and adolescents (and 23% of the adults) in the world do not meet the recommendations on physical activity levels and healthy eating, for example, fruit and vegetable intake [8]. In this regard, a dose-response relationship was detected, with even slight increases in physical activity leading to physiological and psychological health benefits in adults [9-11] as well as in children and adolescents [12]. Longitudinal studies have shown that behavioral patterns in adolescence have low-to-moderate influence on physical activity patterns in adulthood [13-16]; therefore, there is a need for interventions targeting children to promote a sustainable and healthy lifestyle.

Health-related behaviors such as physical activity and healthy eating are embedded in social contexts such as the family context and are affected by social relations and ties [17]. Therefore, addressing behavioral changes embedded in daily family life might be a promising avenue for facilitating an individual’s behavior change. Family meals, for example, are often an important part of everyday life in families and there is accumulating evidence that this collective behavior is associated with a better overall diet quality and body mass index [18-20]. In a similar vein, there is some evidence that family-based physical activity is positively associated with individual physical activity levels [21]. It has been shown that supportive interactions within a family and shared values about health behavior affect children’s physical activity engagement [22] and eating behavior [23]. Moreover, results of intervention studies indicate that social support is significantly associated with continuation of exercise programs [24-28] as well as participation in weight-loss interventions [29-31].

Mobile health (mHealth) technologies are increasingly used as a delivery mode for health behavior change interventions throughout the lifespan. Specifically, smartphone-based apps offer a great promise for enhancing physical activity and healthy eating as well as for making health care more accessible and scalable, more cost-effective, and more equitable [32,33]. Reviews and meta-analyses support the view that app-based mobile interventions are effective and highly promising for changing physical activity [27,34] and nutrition behaviors [35]. Moreover, a recent systematic review of economic evaluations of mHealth solutions found a consistent overall reporting of positive economic outcomes (eg, increase in life-years gained, cost savings, cost-effectiveness) [36].

Reviews on mHealth interventions indicate that the strategies or the central “building blocks” of app-based interventions mainly encompass 4 behavior change technique clusters [37], namely, goal setting, feedback and self-monitoring, information, and social support provision, which coincide with successful conventional individual and group-based interventions [35,38,39]. Setting goals, monitoring behavior, receiving feedback, and reviewing relevant goals in the light of feedback are central to self-management and behavioral control, as specified by control theories [40,41] and health behavior theories [42-44]. However, since mobile interventions distinguish themselves by being interactive, adaptive, time-sensitive, and intraindividually dynamic, more dynamic concepts, including the timing of feedback or tailoring tasks and goals to individual progress and capacities as specified in persuasive technology and gamification approaches, might be essential ingredients of effective focused mobile interventions [35]. Moreover, mobile interventions can be delivered within a social system so that all members, for example, of a family, can simultaneously and collectively take part in an intervention and share their goals and progress. However, currently available apps for health promotion are almost exclusively tailored to the individual person [45]. Motivation for behavior performance is higher when the individual is embedded in a social system of mutual appreciation and importance (see self-determination theory [46,47]), which was successfully used in physical activity interventions by enhancing autonomous motivation and fulfilling the 3 basic psychological needs, that is, “autonomy,” “competence,” and “relatedness” [46]. As healthy or unhealthy behavioral patterns are developed and maintained in social contexts, embedding an mHealth intervention in a family-based setting and targeting all family members might be promising and corresponds to assumptions of family-as-systems approaches [48]. Families represent natural social systems characterized by supportive interactions and common shared values and should therefore be targeted as a whole to implement sustainable behavior change on the individual as well as the family level. Therefore, the described trials aim at developing a smartphone intervention app that targets the family as a social system of high relevance for its single members.

### Objective

The aim of the SMART*FAMILY* project, consisting of SMART*FAMILY* (SF) and SMART*FAMILY*2.0 (SF2.0) is to develop, refine, and evaluate an mHealth intervention aiming to improve physical activity levels and healthy eating at the individual and family level. The development of the app is based on behavior change theories, including self-determination theory and the use of behavior change techniques. Extending the previous research, the behavior of children *and* parents is targeted in order to induce family-based and individual-based behavior changes. In particular, family members are using the SF app individually and cooperatively. Furthermore, SF and SF2.0 aim to deliver context-dependent interventions and provide support during time periods when needed the most. The first version of the app (SF) will be refined, and motivational and gamification features as well as a just-in-time adaptive intervention (JITAI) approach will be added (SF2.0). The effectiveness of SF and SF2.0 will be evaluated through 2 cluster randomized controlled trials consisting of families (parents and their children).

## Methods

### Study Design

The studies are conducted and described according to the CONSORT-eHealth checklist [49], which can be found in Multimedia Appendix 1. The outline of the SF and SF2.0 trials is presented in Figure 1. In both trials, the assessment of outcomes is identical and is completed at baseline (T_0_) after the 3-week intervention (or no intervention) period (postintervention, T_1_), and 4 weeks after T_1_ (follow-up, T_2_). Each family (parents and children) is invited to the laboratory for an individual introductory session. Each family member receives an accelerometer for physical activity assessment and a daily paper-pencil–based diary assessing type, intensity, duration and joint activities as well as food intake (specifically fruit and vegetable intake) during the first assessment week (T_0_, Figure 1). At the end of week 1 (end of T_0_), they fill in a questionnaire (paper-pencil in SF, web-based questionnaire in SF2.0) and return all the materials to the laboratory. The completion of the questionnaire takes about 20 minutes. Both parents and children complete individual daily diaries and questionnaires. The data of the preintervention (baseline) assessment (T_0_) are analyzed and they serve as the basis for the weekly goal set-up in the intervention group during the following intervention period.

**Figure 1 figure1:**
[figure not shown]
Detailed study design. T0: baseline; T1: after 3 weeks of intervention; T2: Four weeks after T1.

Participants allocated to the intervention group receive smartphones with the preinstalled SF app (SF or SF2.0). We provide all study participants with a study smartphone in order to control for device effects (screen size, Android version, etc) and ensure that the app is fully functioning. Carrying an additional device might pose an additional burden for participants and therefore, great care will be taken to explain the need for a study device in the introductory session. Moreover, previous studies within the SMARTACT consortium, comparing participants who could either use their own smartphone or were provided with a study smartphone to record their diet, showed no differences in terms of engagement [50]. Each smartphone (Samsung Galaxy A5 for SF, Nokia 5 for SF2.0) is connected with an accelerometer (Move 3 [SF] and Move 4 [SF2.0], Movisens GmbH) via Bluetooth low energy. Different from similar mHealth studies, the accelerometer used for the preintervention and postintervention (primary outcome) measurement is also used within the intervention period and provides data used by the app. Since participants monitor their physical activities (based on the data from the accelerometer) and goal progress through the app, an additional commercial device is not necessary for motivating the participants. Data are stored in a local database on the smartphone by using an additional app (Movisens Manager app) developed by the Human-Computer Interaction Group of the University of Konstanz as part of the SMARTACT project. The SF and SF2.0 apps are notified by the Movisens Manager app once new sensor data are available (ie, when the accelerometer is in reach of the Bluetooth low energy connection of the smartphone) and processes this data, thus creating 2 new entries in the database: the received data from the accelerometer and the aggregated value for that day (including accelerometer data and manual input by the participants). The aggregated data are then sent via encrypted HTTPS to the server in Konstanz. From there, data are sent back to all family members’ smartphones, so that individual and collective goal progress can be monitored. The control group does not receive any intervention. Please see Figure 2 for a depiction of the operation principles.

**Figure 2 figure2:**
[figure not shown]
Detailed depiction of the operation principles of the SMARTFAMILY apps.

When starting the intervention, all families of the intervention group are asked to set a collective weekly goal for physical activities, which they want to achieve as a family within 1 week, that is, total steps and total time spent on physical activity per family. In addition, collective family goals are set for activities within the family and healthy eating, ie, the amount of fruit and vegetable intake per family and the number of family meals. It is important to note that every single family member is contributing to the collective family goal through his or her own behavior. In contrast to the set goals related to common recommendations such as 10,000 steps a day or 5 servings of fruits and vegetables per day for individuals, the family sets its own collective goals. In order to facilitate realistic goal-setting at the beginning of the intervention, the family members can rely on the analysis of their individual physical activity level and fruit and vegetable intake assessed during T_0_. The goal-setting process is repeated every week during the intervention period. The only goal-setting instruction given to the participants is the recommendation to set collective family goals for the coming week, which are slightly higher than their current cumulative performance. In SF2.0, an interactive goal-setting coach assists with this decision. This procedure involves usage of behavior change techniques, which will be presented in detail below.

After 3 weeks of intervention (or no intervention) period, a 1-week postintervention measurement (T_1_) with the same procedure as T_0_ starts. Four weeks after completion of T_1_, participants fill in the questionnaire for the last time (T_2_) and return them to the study team in a prepaid reply envelope. In SF2.0, participants can complete all questionnaires pseudonymized on the internet. Validated measures and scales are used (if available), which were adapted from paper-pencil versions for web-based versions to make it easier for participants to complete the surveys. Ethical approval was obtained and data protection was ensured. A closed survey design was used and the usability and technical functionality of the electronic questionnaire were tested. Participants receive analyses of their individual activity patterns for study participation in SF and SF2.0, whereas families in SF2.0 are additionally provided with a 40€ (US $46.8) online shopping voucher and an activity tracker for every child of the family in order to further facilitate physical activity maintenance.

### Eligibility Criteria and Ethical Approval

Families are eligible for inclusion if 1 parent or both parents and at least one child who is 10 years of age or older are living together in a common household. All siblings are invited to take part in the study. All participants have to be used to handle a smartphone and speak, read, and write German fluently. In order to ensure fairness, siblings who do not meet the age requirements in the inclusion criteria also receive the study materials, if deemed feasible.

Full ethical approval was obtained from the University of Konstanz (for the consortium SMARTACT) as well as from the Karlsruhe Institute of Technology (for SF and SF2.0). All participants, children, and legal guardians provide written informed consent prior to commencing the study by signing the informed consent form. Both trials are conducted in accordance with the Declaration of Helsinki.

### Randomization and Blinding

Both trials (SF and SF2.0) are cluster randomized controlled trials with 2 groups: (1) an intervention group receiving the SF or SF2.0 and (2) a nonintervention control group. Recruited families who provide informed consent are allocated to one of the 2 groups prior to recruitment by using a simple randomization procedure for cluster designs [51]. Although the intervention group participants are told about the mHealth nature of the study, control group participants are only told to take part in an epidemiologic assessment of physical activity levels, making it essential to wear the accelerometers 2 times for 1 week and to answer several questions over the course of 10 weeks in order to gain reliable and valid results.

### Participant Recruitment

Participants are recruited in schools, school holiday programs, music schools, and sports clubs via personal communication, newspapers, and email distribution lists of the Karlsruhe Institute of Technology. Power analyses for analysis of covariance with 2 groups and 4 covariates using G*Power [52] yields a total of 52 families with approximately N=156 participants (assuming 3 family members), to find a small-to-medium effect (α=.05, 1-β=.80, Cohen *f*=0.25). In order to increase power and to compensate for potential dropouts, we aim for a total of 60 families per trial. Please see Figure 3 for the planned participant flow for SF and SF2.0.

**Figure 3 figure3:**
[figure not shown]
Planned participant flow and allocation pattern for the cluster randomized controlled trial for SMARTFAMILY and SMARTFAMILY2.0.

### Development of SF Apps

Both SF and SF2.0 are developed as part of the SF project, which is part of the consortium project SMARTACT and its toolbox encompassing mobile interventions for promoting physical activity and healthy eating (see for example [53-57]). The multidisciplinary team includes professionals with expertise in sports and exercise science, nutrition, health psychology, neuroscience, economics, and human-computer interactions. SF and SF2.0 are devised in iterative processes, with input from target group members and experts as well as from previous SMARTACT project findings and behavioral theories. Programming of the apps is conducted by the Human-Computer Interaction Workgroup of the University of Konstanz as part of the SMARTACT project, which is responsible for all tasks related to computer science (ie, programming of apps, surveillance of data servers, etc). In general, all people with data access signed a confidentiality agreement. Both apps run on Android and use the SMARTACT Toolbox, which is conceptually developed by the SMARTACT consortium partners [53] and programmed within the SMARTMOBILITY project led by the Human-Computer Interaction Group of the University of Konstanz. The appearance and content of SF and SF2.0 are adapted and changed in iterative processes throughout the invention phases and pilot studies but not throughout a trial. Both apps are piloted for probing usability and feasibility through standardized interviews (SF) and questionnaires (SF2.0).

### Intervention: SF and SF2.0 Apps

Overall, SF and SF2.0 aim to enhance physical activity levels and healthy eating at the family level, including parents and children. The apps are designed to be implemented autonomously by participants. Both apps (SF and SF2.0) are entitled to fulfil criteria of high quality regarding theoretical and empirical foundation [38,46,48]. The inclusion of 10 (SF) and 13 (SF2.0) behavior change techniques doubles the amount of behavior change techniques found in “average” mHealth intervention apps.

### Features of the SF App

Examples of the SF app screens are shown in Figure 4. On the home screen, the app always displays the whole family’s current status of goal achievement as well as individual family member’s contribution (Figure 4, #11-12). During the course of 1 week, if milestones of 25%, 50%, 75%, and finally 100% of goal achievement is reached by the family, every family member receives a congratulatory message and a motivational reinforcement, that is, “Great! You’ve reached 75% of your goal. Go on, you are making a good progress.” Moreover, the detailed goal achievements concerning moderate and vigorous physical activity and steps (Figure 4, #1-7) as well as fruit and vegetable intake (not displayed) on family and individual basis can be examined. The achieved values for specific days are also presented in the calendar function (not displayed). Although physical activity is recorded automatically by the accelerometer, fruit and vegetable intake has to be entered manually into the app (Figure 4, #15). In case of physical activity that is not assessed by the accelerometer because it cannot be worn (eg, swimming) or cannot be validly captured by the hip-worn accelerometer due to a lack of lower body movements (eg, upper body strength exercises or bicycling), the app incorporates a feature to manually enter the individual amount of time spent with moderate or vigorous activity (Figure 4, #8-10). As the family members’ smartphones are connected with each other (via internet) and each smartphone is connected with its accelerometer (via Bluetooth low energy), all family members receive real-time feedback on individual and family-level physical activity behavior with respect to steps, moderate and vigorous physical activity, as well as on self-reported fruit and vegetable intake. This allows for continuous self-monitoring of behavioral goals of a family.

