To further increase motivation, SF2.0 comprises a more detailed gradation of goal achievement. Participants can gather stars for every 10% of goal achievement. If the family achieves their individual goal during 1 intervention week, they are instructed to set a higher goal for the next week. In SF2.0, the interactive goal-setting coach advises them about a promising goal for the following week. If the family does not achieve its individual goal, the coach instructs family members to set the same or even a slightly lower goal for the next week. For recording of the different parameters and operation principles of SF2.0, see SF. One additional feature included in SF2.0 is adapted from the SMARTACT Toolbox [53-55]. Here, users are instructed to take a picture of every single meal (including snacks), producing an exact timestamp of food consumption (Figure 5, #25). Furthermore, SF2.0 comprises a real-time assessment of mood, exhaustion, and stress (Figure 5, #14-16), a gamification approach (visualized by the personal coach and collectable stars; Figure 5, #1), an inactivity-triggered ecological momentary intervention (Figure 5, #17,18), and a provision of up to 5 health-related facts by the interactive coach to improve health literacy [60]. These additional features are related to the inclusion of further behavior change techniques as shown in Table 1.

**Table 1 table1:** Implementation of the basic psychological needs and behavior change techniques within the app features.

Self-determination theory, basic psychological needs	Autonomy	Relatedness	Competence

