#### Primary Outcomes

Primary outcome measures are device-based measured physical activity (ie, amount of steps taken, minutes of moderate-to-vigorous physical activity) via accelerometers (T_0_ and T_1_) as well as self-reported assessed physical activity levels via questionnaires (T_0_-T_2_) and diary records (T_0_ and T_1_). Furthermore, healthy eating (fruit and vegetable intake) is assessed via questionnaires (T_0_-T_2_) and diary records (T_0_ and T_1_). Primary outcomes are similar for SF and SF2.0.

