A constraining factor might be that family sizes and ages within families may vary. As studies have shown that there is an inverse relationship between family size, parental resources, and children’s educational performance [87], family size might also affect intervention success. However, there is currently a lack of knowledge about this relationship regarding behavior change or accomplishment of healthy lifestyles in families. Depending on family size distribution, families of different sizes will be compared if possible. However, future studies need to focus on and examine whether bigger families have advantages or disadvantages regarding intervention effects compared to smaller families. A further constriction might be the age range, especially of children and adolescents. Since this study includes the whole family, children of different ages and with different needs and perceptions are addressed in a similar way by the app, which might affect the intervention effects. Finally, SF and SF2.0 are based on sophisticated technical issues. EMA is used to assess physical activity (accelerometers), healthy eating (diaries), and psychosocial correlates. The inclusion of device-based and self-reported measures of physical activity provides a more comprehensive picture of the actual amount of physical activity. However, the synchronization of accelerometer-based data among multiple users also enhances the complexity of the app and is a potential source of problems caused by the Bluetooth low energy interface.

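### Self-reported activity and diet are primary outcomes on a par with accelerometry, yet only the unmasked arm logs intake and sees its activity data between T0 and T1, so a self-report contrast can mix reporting with behaviour

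*Protocol article*

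**What the plan says.** **Outcomes.** The Primary Outcomes section of the protocol article lists accelerometer steps and moderate-to-vigorous minutes (MVPA) at T0 and T1, and self-reported activity by questionnaire (T0 to T2) and diary (T0, T1). For diet it says "healthy eating (fruit and vegetable intake) is assessed via questionnaires (T_0_-T_2_) and diary records (T_0_ and T_1". No order of importance is given. Data Analysis applies one mixed-model analysis of covariance, time by group, to device and self-report outcomes alike. The Abstract presents the results as the main effects of the intervention.

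**Exposure.** From the Abstract: "The intervention group uses the app for 3 consecutive weeks, whereas the control group receives no treatment". During those weeks "fruit and vegetable intake has to be entered manually into the app", and "all family members receive real-time feedback on individual and family-level physical activity behavior with respect to steps, moderate and vigorous physical activity" (both from Features of the SF App). In SF2.0 "users are instructed to take a picture of every single meal (including snacks" (Features of the SF2.0 App). For the comparator, Study Design says "The control group does not receive any intervention".

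**Knowledge of purpose.** Under Randomization and Blinding, "the intervention group participants are told about the mHealth nature of the study", while controls are told only of a survey of activity levels.

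**Nearest safeguard.** The strengths and limitations section says that having device and self-report measures together "provides a more comprehensive picture of the actual amount of physical activity". Potential Methodological Issues covers duration, follow-up timing and device burden, but not differential reporting.

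**The concern.** Part of the intervention is practice at counting and reporting the quantities that are later self-reported as outcomes. Logging portions, and seeing measured minutes beside one's own impression of the day, can change how a person fills in a diary or questionnaire even if behaviour stays the same. Knowing the purpose of the study can do so too. All of this acts in one arm only, so randomization does not balance it, and the group-by-time term cannot separate it from real change.

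Two conclusions have nothing else to rest on. The first is healthy eating, a primary outcome without an objective measure. The second is maintenance, one of the three questions in the Discussion, because T2 has questionnaires only.

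**Working it through.** **Step 1. What differs between arms before the T1 self-report?**

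| Element | Intervention | Control | Section |
|---|---|---|---|
| Diary at T0 and T1, with fruit and vegetable portions | yes | yes | Study Design; Fruit and Vegetable Intake |
| Three weeks of app logging of intake | yes | no | Features of the SF App |
| Real-time view of steps and active minutes | yes | no | Features of the SF App |
| Told of the app purpose | yes | no | Randomization and Blinding |
| Family goal described for the T1 week | no | no | Study Design |

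Diary practice is shared. What is unbalanced is the exposure between the two diary weeks, together with knowledge of the purpose.

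**Step 2. Which outcomes have an independent check in both arms?** Activity at T1 has the accelerometer. Diet has none: the SF2.0 food frequency items are also self-report, and the meal photographs are taken within the app, so controls have none. T2 has no device measure.

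**Step 3. How large could this be?** The documents give no figure for a reporting shift. The range below is an assumption.

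Planning inputs (Participant Recruitment): two groups, four covariates, alpha 0.05, power 0.80, f = 0.25, 52 families, about 156 participants. Equal allocation is assumed. With noncentrality N f², numerator df 1 and denominator df N − 2 − 4, these inputs need N = 128; at N = 156 the power is 0.873. The stated 156 is therefore not reproduced by this route. The point does not depend on it, and 156 is used below as the plan's own size.

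For two equal groups f = d/2. With no true behaviour change and a reporting shift of d SD in one arm:

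| Shift d | f | Share of planned 0.25 | N f² at N = 156 | P(significant), no clustering | P(significant), ICC 0.3 |
|---|---|---|---|---|---|
| 0.1 | 0.05 | 20% | 0.39 | 0.095 | 0.078 |
| 0.2 | 0.10 | 40% | 1.56 | 0.237 | 0.164 |
| 0.3 | 0.15 | 60% | 3.51 | 0.461 | 0.311 |

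The last column uses an effective N of 156/(1 + 2 × 0.3) = 97.5, for three members per family and an assumed ICC. The nominal rate is 0.05.

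The shift can also go the other way, since device feedback may correct over-reporting. If the true effect is d = 0.50 and intervention reports fall by 0.1, 0.2 or 0.3 SD, the apparent effect is 0.40, 0.30 or 0.20. At N = 156 without clustering it is detected with probability 0.699, 0.461 or 0.237, instead of 0.873.

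These are single-contrast approximations. They show sensitivity and do not estimate bias in this trial.

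**The case against.** The strongest reply is that unmasked behavioural trials with self-report always carry this limitation, and that a sensitivity analysis of this kind normally sits in an analysis plan, which is not shown. The device outcomes are listed first, the Abstract already labels fruit and vegetable intake as self-reported, and both arms keep the same diaries. This stands in part: the absence of a sensitivity analysis is not in itself a fault of the article. What remains is what the article does fix, namely unranked primary status and one common analysis for outcomes whose reporting is rehearsed in one arm only.

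A reader might go further in four ways that the documents do not support.

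- *That a positive self-report result would be spurious.* The direction is unknown, and a real effect could equally be hidden.
- *That reports at T1 are pulled toward the family goal.* Goals are set weekly within the intervention period, and none is described for the T1 week.
- *That the plan calls self-report as accurate as the device.* The sentence on a fuller picture concerns the two kinds of measure together.
- *That diary minus accelerometer minutes measures reporting error.* Features of the SF App says that the hip device cannot be worn for swimming and does not validly capture cycling or upper-body strength work. A real rise in these would widen the gap with no change in reporting. For the same reason, a rule that disowns every self-report difference without a device difference could discard real change.

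**Conclusion.** The concern holds in a limited form. The one-arm exposure, the different information given to the arms, and the equal standing of self-report among the primary outcomes are all in the text. It follows that a self-report contrast at T1 or T2 can mix reporting with behaviour. It does not follow that it will, or by how much: the 20% to 60% of the planned effect is only the assumed 0.1 to 0.3 SD divided by 0.50 SD.

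The activity conclusion at T1 is protected if accelerometry leads it. The diet conclusion and the T2 conclusion have no such protection and can support statements about reported behaviour only. This deserves a change before analysis; it does not undermine the trial.

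**What to change.** 1. Let accelerometer steps and MVPA lead the physical activity conclusion, with self-reported activity as supportive.
2. Add a sensitivity analysis comparing between arms the T0-to-T1 change in diary minus accelerometer MVPA, with an interval that allows for family clustering. Use device-only data: Study Design describes a daily app value that combines sensor data with manual entries, and those entries should stay out. Exclude diary activities the device cannot capture (swimming, cycling, upper-body strength work, sports played without the device). The diary records type, duration and intensity, so this is feasible. Treat an arm difference as a signal of differential reporting, not proof.
3. If self-reported activity differs by arm and accelerometry does not, report it as a difference in reported activity, and show separately the activities the device cannot capture.
4. Word the fruit and vegetable and T2 maintenance conclusions as reported intake and reported activity, and name possible differential reporting as a limitation. Do not adjust T2 questionnaire results by the T1 diary shift: the instruments differ, and there is no diary at T2.

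The cost is one further analysis and narrower wording. No new measurement is needed, so the change can serve both SF, where data collection has stopped, and SF2.0. The price is a less favourable claim if only self-report is positive. For diet, the change narrows the claim but supplies no check.
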